Traditionally, the degree of stenosis in an untreated carotid artery was measured with conventional digital subtraction angiography (DSA). Because of a small but non-negligible risk of stroke or death, DSA has been replaced by non-invasive tests, such as duplex ultrasound (DUS), CT angiography (CTA) or MR angiography (MRA) [8-10]. In the follow-up of patients with a stent, DUS is often used to monitor the patency of the stent and the occurrence of in-stent restenosis. For routine evaluation of un-stented carotid arteries, DUS is a well validated diagnostic test and the cut-off criteria for the different degrees of stenosis are clear [8,9]. For measurements within stents, however, these criteria may not suffice.

In a stenosed artery, narrowing of the lumen results in higher blood flow velocities at that point. Estimating the degree of stenosis with DUS is based on this principle. The peak systolic velocity (PSV) is the best predictor for the severity of the stenosis [11]. However, the degree of restenosis in a stented carotid artery, measured according to the North American Symptomatic Carotid Endarterectomy Trial (NASCET) criteria on CTA or MRA, is often less severe than expected based on the PSV in the DUS test. Possibly, blood flow and blood turbulence behave differently in an artificial stent than in a normal vessel. This problem has been addressed in literature before; particularly by Lal en coworkers [12]. An un-stented carotid artery is likely to have a more elastic vessel wall than a stented one, even if stenosis is present. The cut-off criteria for the degrees of an in-stent stenosis, based on blood velocity parameters, are probably different from the established cut-offs used for un-stented arteries. We hypothesise that the PSV raises more in a stented than in a un-stented carotid artery with a similar degree of stenosis (figure 1). Additional duplex characteristics may also be different in an in-stent restenosis, such as formation of intimal hyperplasia instead of atherosclerotic plaque as cause of the stenosis. These characteristics need to be studied as well; the present study, however, will be limited to definition of PSV criteria. Routine criteria can not be applied to stented arteries but new criteria need to be established for this particular purpose.

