## Results

We identified 6 unique diagnostic series on in-stent stenosis measurements with DUS compared to a reference test (CTA or DSA) [13-18]. In one study DUS and CTA were compared for in-stent measurements, but this paper needed to be excluded because no new criteria were calculated [18]. Additional file 1: Table S1 summarises the 5 series that propose new criteria. In general, the cut-off values are higher than those reported for unstented arteries. For example, the PSV cut-off value for the diagnosis of a >70% stenosis varies between 300 and 450 cm/sec. The reported prevalence of in-stent restenosis was low, which is likely to reflect limited follow-up. Furthermore, the reference test was only performed in these previous studies if stenosis was found on DUS, introducing verification bias. Lal *et al *recently reported a relatively large population of 255 CAS procedures [14]. They confirm overestimation of the degree of in-stent restenosis if regular DUS criteria are applied. Comparisons were made with CTA and DSA. During follow-up, patients underwent DSA only if they were suspected as having restenosis on DUS. Criteria calculated from these data may suffer from verification bias. All patients in their series underwent CTA at the end of their follow-up. The latter data should not suffer from verification bias. In another recent series of Aburahma *et al*, selection was made with DUS and only patients with symptomatic ≥ 50% stenosis or asymptomatic ≥ 80% stenosis were included in their diagnostic study [13]. Applying their DUS criteria to all stented patients is probably not correct because of the selection criteria applied. Zhou *et al *published a large series but concluded that they infrequently found cases of severe stenosis after CAS, and that a multicentre study is warranted to establish reliable in-stent DUS criteria [15]. Only Kwon *et al *reported a series of patients all undergoing both DUS and the reference test, CTA. This study, however, was too small (n = 27) to provide new in-stent cut-off criteria [18].

It is clear from the published data that only small and preselected populations with in-stent restenosis have been studied to date. A large study with sufficient patients with restenosis is therefore needed, as authors of the listed papers also recognised.

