Crucial is the fact that we can compare DUS results to a technique that provides clear images of the lumen, in order to investigate if the PSV raises more in a stented artery than in an unstented artery when the remaining lumen is the same as. Because patients will be recruited from multiple centres, the CT scanners will not be identical and we can only handle this limitation by using comparable scan protocols and similar post-processing techniques. Also, different types of stents will be used. If these stents do not have the same physical properties, the PSV's are perhaps slightly different as well [21]. We shall collect data about the used stents, and in our analyses we shall investigate if there is a relation between type of stent and blood flow parameters. However, the advantage of a multi-centre study is that the results will be widely applicable.

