### Data analysis

Receiver operating characteristics (ROC) curves will be constructed for the diagnoses of 70%–99% and 50%–69% stenosis. The associated optimal sensitivities, specificities, and peak-systolic-velocity thresholds will be derived from the ROC curves. The main result of the analyses will be optimal cut-off points of duplex for in-stent restenosis (not the diagnostic accuracy of duplex) within the context of the present study.

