## Discussion

Carotid angioplasty with stenting (CAS) is being evaluated in ongoing randomized trials. An important factor in the evaluation of carotid artery stents is the degree of possible in-stent restenosis. DUS is a fast and easy test to asses the degree of stenosis. Whereas this diagnostic tool is well validated for stenosis measurements in un-stented carotid arteries, precise cut-off criteria for stented carotid arteries are not available yet. The aim of the proposed study is to validate the use of DUS for in-stent stenosis measurements during follow-up after CAS and to determine reliable cut-off criteria for the different degrees of stenosis. Valid criteria are needed for future research and clinical decision making in patients treated with a carotid artery stent. In conclusion, the ongoing ICSS study provides a unique opportunity to obtain valid DUS in-stent criteria in a sufficiently large population, with a long follow-up and expected high prevalence of restenosis. Verification bias will be avoided by performing both DUS and CTA in all patients. Afterwards, our data will be pooled with other studies, taking into account the limitations of individual studies.

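### The analysis derives new in-stent PSV cut-offs but does not plan to test the routine or published cut-offs in the same fully verified patients, so as planned it does not show that a new cut-off is needed or better

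*Protocol article*

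**What the plan says.** All references are to the protocol article.

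- **Background** first hedges: in-stent cut-offs "are probably different from the established cut-offs used for un-stented arteries". It then states the hypothesis, "We hypothesise that the PSV raises more in a stented than in a un-stented carotid artery with a similar degree of stenosis", and ends firmly: "Routine criteria can not be applied to stented arteries but new criteria need to be established for this particular purpose".
- **Results** (the literature review) says that "the PSV cut-off value for the diagnosis of a >70% stenosis varies between 300 and 450 cm/sec" and attributes verification or selection problems to most of these series. It also cites one series of 255 procedures that found overestimation with regular criteria, and it accepts that this series' end-of-follow-up CTA data should be free of verification bias.
- **Protocol for proposed diagnostic study** gives every participant both duplex and CTA, whatever the duplex result.
- **Reference test** says the CTA comparison is made "in order to investigate if the PSV raises more in a stented artery than in an unstented artery" when the remaining lumen is equal.
- **Data analysis** plans ROC curves for 70–99% and 50–69% stenosis, from which optimal sensitivities, specificities and PSV thresholds are read. It then fixes the priority: "The main result of the analyses will be optimal cut-off points of duplex for in-stent restenosis (not the diagnostic accuracy of duplex".
- **Meta-analysis** pools the completed study with the published ones and models study quality, including verification bias.
- **Discussion**: "The aim of the proposed study is to validate the use of DUS for in-stent stenosis measurements during follow-up after CAS", and to determine cut-off criteria.

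**The concern.** Two sets of existing criteria bear on the study question: the routine un-stented PSV criteria and the published in-stent cut-offs. The article doubts the first and considers most of the second distorted. This cohort is designed to be free of that distortion, so it is the natural place to see how both perform. The stated analysis does neither. It derives a further threshold from the data.

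A clinician or trialist reading the result must decide whether to abandon the routine criteria and, if so, for which value. The published values for stenosis above 70% span 450 − 300 = 150 cm/sec, a ratio of 450/300 = 1.5. A new number on that scale, reported with the sensitivity and specificity it attained in the data that produced it, does not settle either question.

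**Working it through.** **1. The plan's own figure.** Inputs from Sample size: sensitivity 0.90, a 10% interval, prevalence 20% or 10%. The 95% level is assumed. With N = 1.96² × Se × (1 − Se) / (d² × prevalence):
- d = 0.10 (half-width): 1.96² × 0.09 / 0.01 = 34.57 restenoses. Dividing by 0.20 gives 172.9 (stated 172). Dividing by 0.10 gives 345.7 (stated approximately 350).
- d = 0.05 (10% as full width) would give 692 and 1,383, so the half-width was used.

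The figure reproduces. It sizes the study for one sensitivity at one threshold and makes no allowance for choosing that threshold from the data.

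**2. Why the derived cut-off's accuracy cannot settle the question.** Write J = sensitivity + specificity − 1 (Youden index). The derived cut-off maximises J over all thresholds in the sample, and a fixed cut-off is one of those thresholds. In the same data the derived cut-off therefore never scores lower.

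The size of this effect was simulated with 3,000 samples per setting. Assumptions: PSV normal with equal variance in stenosed and non-stenosed arteries; a fixed cut-off that is truly optimal, with Se = Sp = 0.80 or 0.90; the new cut-off chosen by maximum J; N = 300, the article's minimum enrolment.

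| True Se = Sp | Prevalence | New cut-off looks better | Mean apparent gain in J | Mean true change in J |
|---|---|---|---|---|
| 0.80 | 10% | 98.1% | +5.0 points | −1.8 points |
| 0.80 | 20% | 97.8% | +3.6 points | −1.2 points |
| 0.90 | 10% | 96.9% | +3.8 points | −1.6 points |
| 0.90 | 20% | 95.7% | +2.6 points | −1.0 point |

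An apparent gain of this size is thus what would be seen when there is nothing to gain.

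**3. What a comparison of fixed cut-offs could deliver.** Cut-offs on one PSV scale are nested: the higher one can only raise specificity and lower sensitivity. The difference in sensitivity is the share of stenosed arteries with PSV between the two values, with half-width 1.96 × √(p(1 − p)/n). For N = 300:
- Specificity gain of 10 points (assumed): 1.96 × √(0.09/270) = 3.6 points at 10% prevalence; 1.96 × √(0.09/240) = 3.8 points at 20%.
- Sensitivity loss of 5 points (assumed): 1.96 × √(0.0475/30) = 7.8 points at 10% prevalence; 1.96 × √(0.0475/60) = 5.5 points at 20%.

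The specificity comparison is informative; the sensitivity comparison is imprecise. Nesting also makes separate McNemar tests unsuitable. All discordant pairs fall on one side, so six of them already give an exact p of 2 × 0.5⁶ = 0.03, which shows only that some patients lie between the cut-offs.

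**4. Precision at 70–99%.** The roughly 35 cases in step 1 are restenoses of at least 50%. Cases of at least 70% are a subset. If they are a fraction f of those cases, the planned half-width becomes 10/√f points: 14 points for f = 1/2 and 20 points for f = 1/4. Both fractions are assumptions, since the article gives none.

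**The case against.** The strongest case against has four parts.

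- **This is a condensed article.** Patients says the full sub-study protocol is available separately, and that document may contain the comparison. Naming a main result does not exclude secondary ones. This is fair and limits the point to what the article states. But the article is not merely brief here: it chooses its main result, and that result does not answer its own hypothesis.
- **The data are not lost.** A reader might infer that the study *cannot* show whether new criteria are needed. The documents do not support that. PSV and CTA are obtained in every patient, and a PSV ROC curve contains the operating point of every fixed PSV threshold. The gap lies in the planned analysis.
- **The premise has support.** A reader might infer that the failure of routine criteria is purely presumed. Background is hedged in places, and Results cites a series whose CTA data the article accepts as free of verification bias. This stands, although the article still judges the existing evidence to come from small and preselected populations.
- **Accuracy and bias are not ignored.** Sensitivities and specificities will be derived, and Meta-analysis will examine the effect of verification bias. So it would be wrong to infer that accuracy is dropped or that biased data are simply pooled. Neither step, however, compares cut-offs within the same patients.

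**Conclusion.** The point holds in this form: the stated analysis does not evaluate the routine or published cut-offs in the one cohort built to judge them without verification bias, so as planned it does not show that a new cut-off is needed or better. It should be corrected before the data are analysed, but it is not a flaw in the data collection.

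The sizes rest on assumptions. The apparent gain of 2.6–5.0 points against a true loss of 1.0–1.8 points assumes equal-variance normal PSV, selection by the Youden index, and a fixed cut-off that is already optimal. If existing cut-offs are truly far off, a derived one may be truly better; the simulation shows only that its apparent advantage is not evidence of this. The article gives no numeric routine criterion, so no accuracy for it can be calculated here.

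A reader might also carry the planned ±10 points over to the 300–450 cm/sec cut-offs. Sample size does not support that: its cases are restenoses of at least 50%, those cut-offs are for stenosis above 70%, and precision there will be poorer.

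**What to change.** Add to Data analysis:

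1. List the routine un-stented PSV criteria and each in-stent cut-off in Table S1 as numbers, fixed before analysis. Apply each to all duplex–CTA pairs at the stenosis threshold it was meant for, and report sensitivity and specificity with 95% confidence intervals.
2. Compare them with the new cut-off on one pre-stated criterion that combines sensitivity and specificity, such as the Youden index or a weighted misclassification rate. Do not use separate McNemar tests.
3. Use optimism-corrected estimates for the new cut-off (bootstrap or cross-validation that repeats the choice of threshold in each resample). If the best of the published cut-offs is singled out after seeing the data, treat that choice the same way.
4. State that the ±10-point precision refers to restenosis of at least 50% and is not claimed for 70–99%.

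The cost is a little extra analysis on data already being collected, with no further patients or tests. The drawback for the authors is that existing cut-offs may do as well, which would weaken the case for new criteria. The sensitivity comparison will also remain imprecise.

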### Meta-analysis

When the present study is completed, we will pool our data with the other diagnostic studies on this particular topic available in literature [13-18]. In addition to pooled weighted estimates of the overall diagnostic accuracy, the data will be modelled using summary ROC analyses. With this model it will be possible to investigate the effect of important quality criteria of the individual studies on the diagnostic accuracy, such as sample size, duration of follow-up, and presence of verification bias.

## Discussion

Carotid angioplasty with stenting (CAS) is being evaluated in ongoing randomized trials. An important factor in the evaluation of carotid artery stents is the degree of possible in-stent restenosis. DUS is a fast and easy test to asses the degree of stenosis. Whereas this diagnostic tool is well validated for stenosis measurements in un-stented carotid arteries, precise cut-off criteria for stented carotid arteries are not available yet. The aim of the proposed study is to validate the use of DUS for in-stent stenosis measurements during follow-up after CAS and to determine reliable cut-off criteria for the different degrees of stenosis. Valid criteria are needed for future research and clinical decision making in patients treated with a carotid artery stent. In conclusion, the ongoing ICSS study provides a unique opportunity to obtain valid DUS in-stent criteria in a sufficiently large population, with a long follow-up and expected high prevalence of restenosis. Verification bias will be avoided by performing both DUS and CTA in all patients. Afterwards, our data will be pooled with other studies, taking into account the limitations of individual studies.

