**Discussion:**

To address the deficiencies of the existing studies, we propose a prospective cohort study nested within the International Carotid Stenting Study (ICSS), an international multi-centre trial in which over 1,700 patients have been randomised between stenting and CEA. In this cohort we will enrol a minimum of 300 patients treated with a stent. All patients undergo regular DUS examination at the yearly follow-up visit according to the ICSS protocol. To avoid verification bias, an additional computed tomography angiography (CTA) will be performed as a reference test in *all *consecutive patients, regardless of the degree of stenosis on the initial DUS test.

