## Protocol for proposed diagnostic study

To address the deficiencies of the existing studies, we plan to conduct a prospective cohort study nested within the International Carotid Stenting Study (ICSS), an international multi-centre trial in which over 1,700 patients with recently symptomatic internal carotid stenosis have been randomised in equal proportions between stenting and endarterectomy. The ICSS completed recruitment at the end of 2008. The trial protocol specifies annual clinical and ultrasound follow up. A sufficiently large population can be enrolled and because the study is embedded in the ICSS, long term follow-up is guaranteed, allowing us to obtain a larger number of restenoses and therefore more precise estimates for DUS cut-off criteria. Most importantly, during the follow-up all patients in the sub-study will undergo both the reference test of CTA and the test under investigation, regardless of the degree of stenosis on the initial DUS test.

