### Patients

The diagnostic tests will be performed during routine follow-up of the ICSS trial [3]. The inclusion and exclusion criteria are listed in Table 1. In short, all patients with a symptomatic atheromatous carotid stenosis, ≥ 50% by NASCET criteria, suitable for stenting and surgical endarterectomy, can be included for treatment. In addition to the general ICSS criteria, patients are excluded if they have a contraindication for the contrast agent used for the CTA, such as renal failure. In the ICSS, patients have scheduled follow-up visits at 30 days after treatment, 6 months after randomisation and then annually. We will ask all patients who received a stent to participate in this diagnostic study at their follow-up visit 1 year after treatment, or, for patients included more than one year ago, at the first (yearly) ICSS follow-up visit thereafter. A separate informed consent for this diagnostic sub-study informing the patient about the risks of the extra CTA test is obtained. The sub-study has received approval from the Multicentre Research Ethics Committee in the UK. The complete protocol of ICSS and of the present diagnostic sub study is available at: .

**Table 1 T1:** Inclusion criteria International Carotid Stenting Study (ICSS)

Inclusion criteria
- Symptomatic, extracranial, internal or bifurcation, atheromatous carotid artery stenosis that is suitable for both stenting and surgery and is deemed by the randomising clinician to require treatment.
- The severity of the stenosis of the randomised artery should be at least 50% (as measured by NASCET method or non-invasive equivalent).
- Symptoms must have occurred in the 12 months before randomisation. It is recommended that the time between symptoms and randomisation should be less than 6 months, but patients with symptoms occurring between 6 and 12 months may be included if the randomising physician considers treatment indicated.
- The patient must be clinically stable following their most recent symptoms attributable to the stenotic vessel.
- Patients must be willing to have either treatment, be able to provide informed consent, and be willing to participate in follow-up.
- Patients must be able to undergo their allocated treatment as soon as possible after randomisation.
- Any age greater than 40 may be included. There is no upper age limit.
- Patients should only be randomised if the investigator is uncertain which of the two treatments is best for that patient at that time.

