### Sample size

In a sample size calculation in a diagnostic study, in addition to an estimation of the prevalence of disease, a precision of the diagnostic accuracy needs to be defined. We estimate a prevalence of 10 to 20% in-stent restenosis (≥50%) one year after treatment with a stent. To obtain estimates of sensitivity of approximately 90% with a confidence interval of maximally 10%, and a prevalence of restenosis after one year of 20%, we would require a minimum of 172 patients [22]. The estimate of 20% re-stenosis is at the upper limit of the values reported in literature. We used this estimate, because our follow-up interval (after 1 year or more) will be later than of most published numbers. If we use 10% restenosis in the sample size calculation, with similar estimates for sensitivity, specificity, and the confidence interval(s), the number exceeds 300 patients (approximately 350). Because the ICSS included more than 800 patients treated with a stent, and because the follow-up of the ICSS will continue for several years, we expect inclusion of a sufficient high number of patients.

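### The Discussion says verification bias is avoided, but CTA depends on a separate consent that nothing in the article shields from the DUS result

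*Protocol article*

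**What the plan says.** The Discussion makes an unqualified statement: "Verification bias will be avoided by performing both DUS and CTA in all patients". Elsewhere the scope is narrower. Under Protocol for proposed diagnostic study, the promise covers those enrolled: "during the follow-up all patients in the sub-study will undergo both the reference test of CTA and the test under investigation".

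The Patients section sets out how a patient comes to be enrolled:

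- Invitation: "We will ask all patients who received a stent to participate in this diagnostic study at their follow-up visit 1 year after treatment". Those further along are asked later: "for patients included more than one year ago, at the first (yearly) ICSS follow-up visit thereafter".
- Consent: "A separate informed consent for this diagnostic sub-study informing the patient about the risks of the extra CTA test is obtained".

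DUS belongs to the same follow-up. The Abstract (Discussion) says: "All patients undergo regular DUS examination at the yearly follow-up visit according to the ICSS protocol". Protocol for proposed diagnostic study adds: "The trial protocol specifies annual clinical and ultrasound follow up".

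The Abstract sets a minimum of 300 patients. The pool is given under Sample size: "Because the ICSS included more than 800 patients treated with a stent". The only blinding described, under Stenosis measurement, is that of the two CTA readers.

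**The concern.** The Verification bias section defines the bias as arising when the decision to do the reference test depends on the index test. Here that decision has two parts: the investigators' rule, which ignores DUS, and the patient's consent to an extra contrast CTA. The article controls only the first. Consent is sought at a visit that includes DUS, and the order of the two is not given. A patient told that the stent looks narrowed could be readier to accept CTA than one told that it is clear, and a recruiter who has seen the result could press harder.

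If that happened, DUS-positive patients would be over-represented among those verified. Sensitivity would be overestimated, specificity underestimated, and the PSV cut-off moved upward. The cut-off matters most, because Data analysis names it as the main result. An upward shift also runs in the direction of the study's own hypothesis of higher velocities in stented arteries. The Meta-analysis section plans to examine the presence of verification bias across studies, so classifying this study as free of it without a check would carry the error forward.

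**Working it through.** **The plan's own figures.** Sample size gives sensitivity 90%, a confidence interval of at most 10%, and prevalence 20% or 10%. Taking 95% two-sided (not stated) and 10% as the half-width:

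- Cases needed = 1.96² × 0.9 × 0.1 / 0.1² = 34.57.
- N = 34.57 / 0.20 = 172.9 (stated 172); N = 34.57 / 0.10 = 345.7 (stated about 350).

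Both reproduce, so the planned precision is about ±10 points on sensitivity.

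**Room for selection.** At the minimum target, 300 / 800 = 37.5%, so 62.5% or more of the stented pool would have no CTA. This is the position at the floor, not a forecast.

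**Effect on accuracy.** Assumptions not in the article: true Se = Sp = 0.90, 800 patients, prevalence 15% (the midpoint of the stated 10% to 20%), CTA uptake a in DUS-positive and b in DUS-negative patients.

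- Apparent Se = Se·a / [Se·a + (1 − Se)·b]
- Apparent Sp = Sp·b / [Sp·b + (1 − Sp)·a]
- P(DUS+) = 0.9 × 0.15 + 0.1 × 0.85 = 0.22
- Verified = 800 × [0.22a + 0.78b]

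For a = 0.60, b = 0.30: Se = 0.54 / (0.54 + 0.03) = 0.947; Sp = 0.27 / (0.27 + 0.06) = 0.818; verified = 800 × (0.132 + 0.234) = 293.

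| Uptake DUS+/DUS− | Verified | Apparent Se | Apparent Sp | Error Se / Sp (points) |
|---|---|---|---|---|
| equal, 37.5%/37.5% | 300 | 90.0% | 90.0% | 0 / 0 |
| 50%/35% | 306 | 92.8% | 86.3% | +2.8 / −3.7 |
| 60%/30% | 293 | 94.7% | 81.8% | +4.7 / −8.2 |
| 70%/25% | 279 | 96.2% | 76.3% | +6.2 / −13.7 |

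All rows yield roughly the planned 300, so the recruitment total would not reveal the problem. The direction depends on who accepts: uptake of 40%/60% gives 85.7% and 93.1%.

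**Effect on the cut-off.** The article does not say how the optimal threshold is chosen; the Youden index is assumed. Without selection, that cut-off lies where the PSV densities with and without restenosis are equal. With uptake depending on PSV, it lies where their ratio equals mean uptake with restenosis divided by mean uptake without. If uptake rises with PSV, that quotient exceeds 1 and the cut-off moves up.

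Illustrative model (assumed): PSV normal, mean 260 and SD 70 with restenosis, mean 120 and SD 50 without, uptake stepping from b to a at 180 cm/s. Then P(PSV ≥ 180) is 0.873 with and 0.115 without restenosis. For 60%/30% the quotient is (0.873 × 0.6 + 0.127 × 0.3) / (0.115 × 0.6 + 0.885 × 0.3) = 0.562 / 0.335 = 1.68.

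| Uptake | Quotient | Youden cut-off (cm/s) | Shift |
|---|---|---|---|
| equal | 1.00 | about 187 | 0 |
| 50%/35% | 1.31 | about 193 | +6 |
| 60%/30% | 1.68 | about 199 | +12 |
| 70%/25% | 2.13 | about 204 | +17 |

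**The case against.** The strongest reply is that the protocol already deals with the bias as it defines it. All stented patients are to be asked, CTA is done whatever the DUS shows, and the promise is elsewhere limited to sub-study patients. Separate consent is ordinary research ethics. This largely stands: the classic mechanism is gone, and only a conditional risk is left.

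It can also be said that the article condenses a fuller protocol, which may fix the order of consent and DUS. That is fair, and if it does, one sentence here settles that part. The point is not the missing detail, however. It is that the article affirms a conclusion which the steps it describes do not secure.

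Several stronger readings are tempting and are not supported:

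- *Earlier DUS results are known when consent is sought.* No section says who knows them. For patients included more than a year ago an earlier annual DUS is plausible; for those asked at the 1-year visit none is documented. How many fall in each group is not given.
- *Restriction to consenters is itself verification bias.* It is so only if consent tracks DUS. Refusal unrelated to DUS, and exclusion for a contrast contraindication, do not by themselves cause it.
- *Some 60% will go unverified.* The 300 is a minimum, and the eligible pool is also smaller than all those stented.
- *The error exceeds the planned precision.* The sensitivity errors above (2.8 to 6.2 points) are all below 10; only one specificity error, in the most extreme scenario, is larger.
- *Stents that failed before the invitation drop out.* Nothing in the article bears on this, and it would be a different problem.

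Finally, the uptake rates and PSV distributions are assumed, and the shifts of 6 to 17 cm/s are small beside the 300 to 450 cm/s span of published cut-offs for >70% stenosis quoted in Results. That limits the likely size but does not justify the flat claim.

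**Conclusion.** The concern holds in a limited form. The Discussion says more than the described design secures: CTA follows a separate, risk-specific consent sought at a visit that includes DUS, and no stated safeguard covers that decision. Whether bias results depends on a relation between DUS and uptake that the article neither prevents nor plans to examine.

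With no such relation, the bias is zero. With uptake of 50%/35% to 70%/25%, it is +3 to +6 points on sensitivity, −4 to −14 points on specificity, and about +6 to +17 cm/s on the cut-off. These ranges rest on assumed true accuracy of 90%/90%, assumed uptake and an assumed PSV model; they show plausible size, not an estimate. The change is worth making, because the order of consent and DUS cannot be restored after enrolment and avoidance of this bias is the study's main stated advantage over earlier work.

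**What to change.** 1. **Patients:** require that the invitation, and consent or refusal, be recorded before that visit's DUS is performed or disclosed. This does not undo knowledge of an earlier DUS, which is why step 2 is also needed.
2. **Data analysis:** report uptake, and compare routine DUS PSV (current and, where available, earlier) between participants and non-participants. Report cut-offs weighted by the inverse probability of verification as a sensitivity analysis beside the unweighted ones.
3. **Discussion:** limit the statement to consenting patients, and say that verification bias is *reduced* unless these checks agree.

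The cost is a wording change on the order of two steps and a modest extra analysis, with no additional patient or test. The downsides are slightly wider intervals in the weighted analysis, the assumption that uptake depends only on recorded variables, and dependence on ICSS routine DUS recording in-stent PSV for non-participants. The article promises annual ultrasound but does not confirm that last item, so it should be checked first.
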